## **2.10 Data Analysis**

Primary analysis: We will compare the primary outcome between study arms. We hypothesize that presentation at GP practices will be higher in the two intervention arms than in the standard of care arm. We will test for significant differences in the primary outcome between each of the intervention groups and the standard of care group using logistic regression analyses.

Secondary analyses: We will also compare the secondary outcomes in each intervention group to the standard of care group using logistic regression analyses. Our hypothesis is that HIV testing uptake will be higher in the intervention groups than the standard of care group.

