### **1.1 The HIV Care continuum in South Africa: where are the gaps?**

South Africa has built the world's largest HIV treatment program since starting to provide antiretrovirals in 2004. In 2020, there were an estimated 7.6 million people living with HIV (PLHIV) and 5.2 million (70%) were receiving antiretroviral therapy (ART) (1). Yet South Africa, like many countries, did not manage to reach the 90-90-90 targets by 2020 and is unlikely to reach the 95-95-95 targets by 2030 without further progress in expanding the utilization of HIV services. According to UNAIDS, 92% of PLHIV South Africans knew their status in 2020 but of those only 70% initiated treatment and of those 64% were virally suppressed (1). The General Practitioner Care Cell (GPCC) is an innovative, public-private partnership that seeks to increase coverage of ART among PLHIV by leveraging the resources in the private healthcare sector to reach uninsured individuals who are not accessing care.

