### **1.5 Study objectives**

To determine whether HTS demand creation material that leverages behavioural science principles will increase the demand for HIV testing at GP practices.

The primary outcome will be presentation at the GP practice. Secondary outcomes will include HIV testing uptake, yield of new HIV-positive diagnoses, and yield of PLHIV who initiate ART.

This will be a randomized controlled trial to rapidly test two different low-cost demand creation

interventions among adults residing in the catchment areas of GPCC programme clinics. There will be three study groups:

1. For one group of participants, free HIV testing will be bundled with other health services that might be desired. Participants will receive a brochure that advertises the opportunity to receive free blood pressure testing and rapid glucose testing along with free HIV testing (Appendix 1). This approach seeks to address stigma associated with HIV testing while also offering other health services that people value.
2. For a second group of participants, the value of HIV testing will be emphasized using a 100 Rand voucher (US\$ 6.67) that can be redeemed for free services (Appendix 2). This approach highlights the monetary value of the free services and seeks to leverage an endowment effect and loss aversion.
3. A third group of participants will receive the standard of care promotion materials for HIV testing. The standard of care (SOC) community demand procedure includes distributing a Your Care Network (YCN) brochure that advertises free HTS and free ART services for those that test positive (Appendix 3), a website ([www.yourcarenetwork.co.za](http://www.yourcarenetwork.co.za)), a YCN Facebook page and standard signage and posters outside participating GP practices.

We will examine the effect of demand creation interventions on the likelihood that individuals will visit GP practices and utilize HIV services. We will also examine the effect of the interventions on identification of newly diagnosed PLHIV.

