## **2.6 Study outcomes**

The primary outcome for this study will be presentation at the GP practice. For each adult who is enrolled in the study and given information about the GPCC, we will determine whether they presented at one of the GP practices.

Secondary outcomes will include the following:

- HIV testing uptake: We will assess whether participants complete HIV testing at GP practices. This outcome will be defined for all adults who are enrolled in the study.
- HIV-positivity among participants who get tested for HIV.
- Linkage to care among newly diagnosed individuals. We will assess whether participants who tested HIV-positive initiate ART at the GP practices.

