## **2.7 Sample size**

We anticipate that about 5% of participants in the standard of care group will present at the GP. This is a conservative assumption based on the experiences of similar campaigns in which individuals are approached in the community. With 2,400 adults randomized to each of the three study arms (total sample size of 7,200 adults), we will have >80% power (alpha=0.05, 2-sided) to detect a difference of at least 2 percentage points in attendance at GP practices.

However, since there is a possibility that a larger proportion of participants in the standard of care group will present at the GP, we have selected a sample size of 4,000 adults per arm (12,000 total) as this will ensure there is 80% power to detect a difference of at least 2 percentage points.

A small difference in the primary outcome would be meaningful given the low cost of the demand creation interventions. With 5 field workers distributing materials over a period of 10

weeks, ), the target of 12,000 adults reached by the field workers can be achieved by enrolling 48 individuals per day (which is feasible given the small amount of time needed to enrol an individual). HTS services at the GP practice will also start at the same time as the field work but will run for a period of 12 weeks. Provision of services at the GP practices will continue for an extra 2 weeks following the end of field work in order to allow individuals with the marketing material to still access HTS.

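### On the protocol's background figures, ART linkage among newly diagnosed people would rest on about 2 to 5 people per arm, too few for the ordinary logistic regression that section 2.10 plans

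*Protocol*

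**What the plan says.** Section 2.10 sets one method for every secondary outcome: "We will also compare the secondary outcomes in each intervention group to the standard of care group using logistic regression analyses". It makes no exception for sparse outcomes. The only secondary hypothesis it states concerns testing uptake.

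Section 2.6 lists three secondary outcomes: testing uptake among all enrolled adults, HIV-positivity among those tested, and "Linkage to care among newly diagnosed individuals". The sentence after that last item describes the people assessed as participants who tested HIV-positive, which could be a wider group. Section 1.5 adds: "We will also examine the effect of the interventions on identification of newly diagnosed PLHIV".

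Section 2.7 sizes the trial on attendance alone. It states "We anticipate that about 5% of participants in the standard of care group will present at the GP" and plans "to detect a difference of at least 2 percentage points in attendance at GP practices". It raises 2,400 per arm to 4,000 because standard-of-care attendance could be higher than expected. No expected number of diagnoses or ART starters is given.

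Two background figures bear on the yield. Table 1 (section 2.1) applies a provincial HIV prevalence of 12%. Section 1.1 says "92% of PLHIV South Africans knew their status in 2020 but of those only 70% initiated treatment".

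**The concern.** The linkage outcome sits at the end of a chain: present, test, be positive, be newly diagnosed, start ART. Each step shrinks the denominator, and the sample size was set at the first step only. If a handful of newly diagnosed people remain in each arm, one arm will often have all or none starting ART, or nobody in the denominator at all. The maximum-likelihood odds ratio is then zero, infinite or undefined, and the Wald interval and p-value that software prints carry no information. A large standard error and a non-significant p-value from such a fit could be misread as showing no effect on linkage.

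**Working it through.** **The protocol's own figure first.** A two-proportion comparison of 5% against 7% at two-sided alpha 0.05 needs 2,213 per arm. With 2,400 per arm the power is 83.1%, so the stated figure of more than 80% reproduces. With 4,000 per arm it is 96.5% at 5% against 7%, falling to 80.1% at 10.5% against 12.5%. That fits the reason given for the larger size, so both attendance scenarios are carried forward.

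**Inputs.** From the protocol: 4,000 per arm; attendance 5% with a 2-point difference (2.7); prevalence 12% (Table 1); 92% aware and 70% initiating treatment (1.1). Assumed: attenders resemble the background population, all presenters test, and 70% serves as a stand-in for ART start after a new diagnosis.

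**Expected new diagnoses per arm.** There are two ways to count:
- (a) Known positives present and test like anyone else: share newly diagnosed = 0.12 × 0.08 = 0.96%.
- (b) Known positives do not test, so all presenters come from the rest: 0.12 × 0.08 / (1 − 0.12 × 0.92) = 0.0096 / 0.8896 = 1.08%.

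| Attendance | Presenters | New diagnoses (a) | New diagnoses (b) |
|---|---|---|---|
| 5% vs 7% | 200 vs 280 | 1.9 vs 2.7 | 2.2 vs 3.0 |
| 10.5% vs 12.5% | 420 vs 500 | 4.0 vs 4.8 | 4.5 vs 5.4 |

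**Chance of a finite odds ratio.** Both arms need at least one starter and one non-starter. With a Poisson number of diagnoses of mean L and ART start probability p, one arm meets this with probability (1 − exp(−Lp)) × (1 − exp(−L(1 − p))). The two arms multiply.

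Example, 5% vs 7%, count (a), p = 0.7:
- Standard of care, L = 1.92: (1 − 0.261) × (1 − 0.562) = 0.324.
- Intervention, L = 2.688: (1 − 0.152) × (1 − 0.446) = 0.469.
- Product 0.152, so non-finite in 84.8%.

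| Scenario (p = 0.7) | Non-finite (a) | Non-finite (b) |
|---|---|---|
| 5% vs 7% | 84.8% | 80.5% |
| 10.5% vs 12.5% | 51.4% | 44.2% |

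At 50% ART start the 5% vs 7% figures are 79.2% and 73.5%; at 90% they are 96.9% and 95.9%.

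**Sensitivity to the assumptions, at 5% vs 7% and p = 0.7.**
- Only 70% of people with HIV aware: 7.2 vs 10.1 diagnoses, non-finite in 16.4% (a); 7.9 vs 11.0, non-finite in 13.2% (b).
- Denominator of all HIV-positive testers: 200 × 0.12 = 24 vs 280 × 0.12 = 33.6, non-finite in about 0.1% (12.2% at 90% ART start).

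**What a comparison could show even with an exact method.** With exactly 2 and 3 people the smallest two-sided Fisher p is 0.10. Fisher power for ART start of 70% vs 90% is 0.6% at 2.2 vs 3.0 diagnoses, 2.6% at 4.5 vs 5.4, and 9.9% at 7.9 vs 11.0. With 24 vs 34 people, power (two-proportion formula) is 14% for 70% vs 80% and 49% for 70% vs 90%.

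**New diagnoses per enrolled adult.** At 5% vs 7%, at least one arm has none in 20.5% (a) or 15.9% (b) of trials. A finite odds ratio therefore exists in about 80-84%. Fisher power is about 1 to 1.5%.

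**The case against.** **The method may be settled elsewhere.** Handling of sparse outcomes is often left to a statistical analysis plan, and the protocol names neither unpenalised maximum likelihood nor Wald tests. Firth's method is itself a form of logistic regression. This stands in part: a plan not shown here could resolve the matter. But the protocol does fix a method for all secondary outcomes, and that wording, read in the ordinary way, fails for this one.

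**The inputs are not a forecast for attenders.** The 12% is provincial and the 92% national, and people who respond to an offer of HIV testing may differ. This stands. The protocol prints the inputs but not the yield, and with 70% aware the failure drops to about 13-16%.

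**Attendance may be higher, and the denominator wider.** Both stand. At about 10.5% attendance the failure affects roughly half of trials. With all HIV-positive testers as denominator it nearly vanishes at 70% ART start.

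Three stronger readings are tempting but not supported:
- A reader might infer that the estimate usually fails whatever the circumstances. That holds only at about 5% attendance, with the newly-diagnosed denominator and attenders who mirror the background population.
- A reader might infer that logistic regression also fails for HIV-positivity or new diagnoses. It does not: about 24 vs 34 positives among testers cause no estimation problem, and new diagnoses per enrolled adult usually give a finite estimate. The difficulty for new diagnoses is very low power.
- A reader might infer that section 1.5 promises to demonstrate an effect on diagnoses. It says only that the effect will be examined, and no power is claimed for diagnosis or linkage.

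**Conclusion.** The point holds for ART linkage among newly diagnosed people and for that outcome alone. If attenders mirror 12% prevalence and 92% awareness, all test, and 70% start ART, the planned odds ratio is non-finite in about 80-85% of trials at 5% vs 7% attendance and about 44-51% at 10.5% vs 12.5%. How often it fails depends strongly on awareness among attenders and on which denominator section 2.6 intends. The low information does not: in every scenario examined, power for linkage differences of 10 to 20 percentage points stays below 50%, and it is under 3% on the protocol's background figures. This is a moderate issue in a secondary outcome. Presentation, testing uptake and the attendance power claim are not in question.

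**What to change.** - **Section 2.10, linkage only:** replace ordinary logistic regression with counts per arm, exact 95% intervals for each proportion, and a Fisher comparison of each intervention arm with standard of care. If an odds ratio is wanted, use Firth-penalised logistic regression. State that linkage is descriptive and that a non-significant result will not be read as no effect.
- **Section 2.6:** choose one denominator for linkage, either newly diagnosed participants or all who test HIV-positive, and use it in both sentences.
- **Other outcomes:** keep logistic regression for presentation, testing uptake and HIV-positivity. Add a sentence saying that comparisons of new diagnoses will have very low power.

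The cost is a few sentences, with no extra participants or data. The downside is that linkage is openly labelled descriptive.

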## **3. ETHICAL CONSIDERATIONS**

### **3.1 Informed consent**

We request that informed consent be waived for individuals who are approached by the YCN field worker in the research based on the following:

**The demand creation activities involve no more than minimal risk to subjects:**

- This request for an informed consent waiver is only applicable to the individuals that the YCN field worker approaches in the field for the purposes of handing out a brochure
- During the field interaction, no personal identifying information will be collected. The distribution log (Appendix 5) that will be completed by the field worker on REDCap when interacting with an individual does not collect any identifying information. This information will only track recruitment indicators from the field
- Demand creation via printed material is a routine activity that is being implemented

already and the study poses no more than minimal risk. Individuals will all receive printed information about the services available to them, but the decision to present for those services is at the choice of the individual

- The demand creation activities involve no more than minimal risk to subjects.
- The demand creation activities could not be carried out practically without the waiver or alteration
- The waiver or alteration will not adversely affect the rights and welfare of the subjects.
- Where appropriate, the subjects will be provided with additional information about their participation
- Individuals who accept the brochure and attend the GP practice to access health services or HIV testing will be invited to sign a written informed consent. Consent will be obtained for study participation and HIV testing.

We will obtain written informed consent from the individuals that present for services at the GP practice for enrolment into the study, in order to extract the necessary data from their medical records and report on the primary and secondary outcomes (Appendix 8 & 9). Consent will be obtained for those attending the GP practice to assess medical records. Following standard GPCC practice when participants present for HTS they will be consented for the medical procedure (Appendix 7).

### **3.2 Ethical review**

The protocol, informed consent forms, other requested documents and any subsequent modifications will be reviewed and approved by the University of Witwatersrand, University of Pennsylvania and Boston University Institutional Review Boards (IRBs) prior to starting this study. We will also obtain approval from the National Health Research Database (NHRD) for district approval. Subsequent to initial review and approval, the ethics board will review the study at least annually. These reports will include changes in the research activity and unanticipated

problems involving risks to study participants or others.

### **3.3 Study benefits**

By taking part in this study, participants will not receive any direct benefits. However, participation in this research could benefit the community as a whole. In this research we will be able to find which are the best ways to give information to individuals that will help to encourage them to seek out and access health services including HIV care and treatment.

### **3.4 Risks**

It is possible that the individuals' visit to GP practice and involvement in the associated research study could become known to others. This could result in social harms (i.e. where others may think that they are HIV-infected or at "high risk" for HIV infection). However, we will take special steps to maintain confidentiality and minimize the risk of social harm. Even though we have systems in place to protect the identity of individuals, there could be accidental disclosure of health data. Some individuals could also experience discomfort during the medical procedures. Individuals that take up the offer of free services may be diagnosed with HIV or other lifestyle conditions. This may cause the individual distress but ultimately early diagnosis allows for treatment and better outcomes.

### **3.5 Study compensation**

Participants in the study will not be provided compensation for taking part in the study.

Participation in the study will be voluntary and participants can opt-out at any point.

### **3.6 Safety and adverse events**

There are no known safety or adverse events of this study. Standard patient care will be followed when individuals access HIV testing services at the GP practice.

### **3.7 Study administration, data handling and record keeping**

Study implementation will be directed by this protocol as well as study-specific procedures.

Standard operating procedures will outline more detailed procedures for conducting this study. Monthly meetings/teleconferences with investigators will occur to review study progress with corrective feedback supplied as necessary to implement the protocol.

We will collect routine demographic information (age, gender, telephone number and primary home address) and HTS outcomes (Date of HIV test, HIV test result and ART start date) from participants who sign the informed consent. We will ask participants these questions to follow up on their results and request permission to access their medical records. As soon as we have the data that we need, we will remove all personal identifiers. No identifiers will be included in any of the data that is analyzed or included in any results.

All confidential patient information regarding HIV status and antiretroviral treatment status and ID will be recorded in the Intelligent Care System (ICS), the GPCC's existing IT platform that includes detailed clinical care plans which are built on the Standard Treatment Guidelines and the Essential Medicine List (EML) and the GPCC-approved medicines and laboratory formularies. The ICS manages all data linked to the individuals/patients (demographics, screenings, clinical care, laboratory services, prescription and dispensing activities) and engagement (date and time) in a secure environment and is implemented real time or near-real time based on paper-based source documents (e.g. HTS consent forms etc.). As part of the GPCC Standard of Care, data are reviewed and verified on a weekly basis with routine random samples to verify patients and data accuracy to source documentation. The ICS system currently generates all data needed for clinical management and routine reporting for the GPCC program and will be used to capture and store HTS screening and ART data for analysis under this research project.

All data are encrypted with password protection, allocated roles and responsibilities per user. Data are longitudinal and linked to named/identified patients and will allow for sophisticated data analysis and summary in line with research requirements. Data extracts are restricted in line with POPIA requirements. Although patient identifiers are captured in the system, data for

purposes of this research project will be extracted, delinked from any patient identifiers and will rely on the ICS system-generated patient number.

Data for monitoring and evaluation of the intervention will be de-identified at the point of data collection.

- The investigator team providing support for monitoring and evaluation of the demand creation strategies will not have access to any information that will identify the individual patients. Further, the investigators will not have access to any patient files. The ICS-generated patient number will serve as the unique study number in the data set.
- GP practices will be assigned a study practice number.
- Field workers and the GPs will collect data that will be used for monitoring and evaluation. This data will be documented on routine systems and study-specific forms that will not contain any information that can identify individual patients.
- After the study consent form is signed, individuals that attend the GP practice for HTS will be given a unique study identifier through ICS. Data collected for this study will be de-identified and cannot be fully anonymised because GPs need to verify whether individuals tested for HIV and were linked to care if tested HIV positive. The link between patient IDs and unique study numbers will be kept by the GP in a locked cabinet at the selected GP practices. In addition, the links will be kept separate from other study documents to reduce the chances of linking the unique study number to the patient's file number.
- In addition to the data being de-identified, we will also aggregate findings when reporting (i.e., no individual cases will be reported on).

The study databases resulting from data collection will not contain identifying information and will be organized by assigned study ID numbers. Databases will be stored on password-protected computers. All database files will also be password-protected, and only study staff will have access to the files. Hard copy documentation will be stored in locked cabinets (at the GP practice overseen by the implementing partner). On completion of the final dataset(s), hard copies of

study documentation will be scanned. The hard copies will then be destroyed, and the electronic copies of the originals will be kept for six years after study completion before destroying them.

### **3.8 Study monitoring**

The study sponsor, University of Pennsylvania (UPenn) may conduct monitoring or auditing of study activities to ensure the scientific integrity of the study and to ensure the rights and protection of study participants. Monitoring and auditing activities may be conducted by:

- Staff (“internal”)
- Authorized representatives of UPenn

Monitoring or auditing may be performed by means of on-site visits or through other communications such as telephone calls or written correspondence. The visits will be scheduled at mutually agreeable times. During the visit, any study-related materials may be reviewed and the Investigator along with study staff should be available for discussion of findings. The study may also be subject to inspection by regulatory authorities (national or foreign) as well as the IECs/IRBs to review compliance and regulatory requirements.

